## Abstract

**Background:**

The therapeutic advances and progress in the care for preterm infants have enabled the regular survival of very immature infants. However, the high burden of lifelong sequelae following premature delivery constitutes an ongoing challenge. Regardless of premature delivery, parental mental health and a healthy parent–child relationship were identified as essential prerogatives for normal infant development. Family centered care (FCC) supports preterm infants and their families by respecting the particular developmental, social and emotional needs in the Neonatal Intensive Care Unit. Due to the large variations in concepts and goals of different FCC initiatives, scientific data on the benefits of FCC for the infant and family outcome are sparse and its effects on the clinical team need to be elaborated.

**Methods:**

This prospective single centre longitudinal cohort study enrols preterm infants ≤ 32 + 0 weeks of gestation and/or birthweight ≤ 1500 g and their parents at the neonatal department of the Giessen University Hospital, Giessen, Germany. Following a baseline period, the rollout of additional FCC elements is executed following a stepwise 6-months approach that covers the NICU environment, staff training, parental education and psychosocial support for parents. Recruitment is scheduled over a 5.5. year period from October 2020 to March 2026. The primary outcome is corrected gestational age at discharge. Secondary infant outcomes include neonatal morbidities, growth, and psychomotor development up to 24 months. Parental outcome measures are directed towards parental skills and satisfaction, parent-infant-interaction and mental health. Staff issues are elaborated with particular focus on the item workplace satisfaction. Quality improvement steps are monitored using the Plan- Do- Study- Act cycle method and outcome measures cover the infant, the parents and the medical team. The parallel data collection enables to study the interrelation between these three important areas of research. Sample size calculation was based on the primary outcome.

**Discussion:**

It is scientifically impossible to allocate improvements in outcome measures to individual enhancement steps of FCC that constitutes a continuous change in NICU culture and attitudes covering diverse areas of change. Therefore, our trial is designed to allocate childhood, parental and staff outcome measures during the stepwise changes introduced by a FCC intervention program.

**Trial registration:**

Clinicaltrials.gov, trial registration number NCT05286983, date of registration 03/18/2022, retrospectively registered, http://clinicaltrials.gov.

## Background

Family centred care (FCC) acknowledges that emotional, social and developmental support are integral components of health care. The respect for the infants’ and the families’ innate strengths are at the core of FCC as well as supporting families in their caregiving and decision-making roles [1]. In 1993 Helen Harrison introduced the principles of FCC in the Neonatal Intensive Care Unit (NICU) [2]. Since that time various FCC initiatives have been implemented, although inconsistently, in NICUs all over the world [3–5].

FCC is more of a concept that needs to be integrated into the culture of the NICU and the attitude of each individual than a set of tasks to be accomplished [6, 7] At the core of FCC is providing healthcare in the context of the strengths and needs of the patients, their family and the community. The goal is to improve quality, psychological wellbeing, clinical outcomes and the overall patient and family experience [6].

Technical and medical advances greatly improved the outcome of preterm infants, especially for the most immature, [8] but NICUs are highly professionalized and often stressful environments for preterm infants and their parents [9]. In spite of these advances neonatal morbidities (e.g. bronchopulmonary dysplasia, retinopathy of prematurity, severe brain injury) continue to affect premature infants and they still have more neurobehavioral problems and a poorer neurodevelopmental outcome than their term counterparts [10, 11]. The stressful NICU environment and the stressful experience of the parents might further aggravate these undesirable outcomes. FCC has been introduced into the care of preterm infants to reduce stress for the infant and the whole family.

FCC interventions and outcomes vary significantly across different studies [12]. Parents were involved in the care to different degrees, ranging from interventions to support parents, interventions that are delivered by parents to concepts that focus on partnering with parents as equal counterparts in the care of their infant [6]. In a recent review FCC interventions improved weight gain, readmission rates and parental satisfaction, however, length of stay and neonatal morbidities were not improved [12]. Family integrated care (FiCare) has been developed in Canada and is currently the FCC programme that has been tested in the largest group of preterm infants with improved infant weight gain and motor development and reduced parental anxiety [12–14]. FiCare is built on four pillars: Parent education, staff education, NICU environment and psychosocial support: [13].

The present study will focus on interventions following the 4 pillar concept.

The primary outcome of the study is length of hospital stay measured by corrected gestational age at discharge. We hypothesize that empowerment of parents and their increasingly active involvement in infant care will reduce length of hospital stay, as parents will be ready to take their infant home earlier [15].

Quality improvement (QI) methods have become a central part of neonatology within the last years. One widely used approach is the Model for Improvement and the PDSA (Plan- Do- Study- Act) cycle (Model for Improvement, Fig. 1) [16].

**Fig. 1 Fig1:**
[figure not shown]
Model for improvement

The Model of Improvement asks three questions: What are we trying to accomplish? (aim) How will we know that a change is an improvement? (measurement) What change can we make that will result in improvement? (wise guess) [16].

The PDSA cycle is a continuous circuit of sequential cycles with the complexity and size of cycles increasing with every cycle [17]. The cycle starts with a change concept (Plan), the next step is the implementation of the new intervention (Do), followed by qualitative and quantitative monitoring and data collection (Study) and the final step of integrating the learning generated which will then lead to acceptance, rejection or adaptation of the intervention (Act), [16] followed by the next PDSA cycle (PDSA cycles, Fig. 2).

**Fig. 2 Fig2:**
[figure not shown]
PDSA cycles

Although widely used in healthcare two reviews of 2014 and 2019 have shown that the five key principles of the PDSA cycle are applied inconsistently with only 3% and 4% of the reviewed studies applying all of the following key principles: sufficient documentation of PDSA cycles, iterative cycles, small-scale-testing, continuous data collection and theoretical rationale [17, 18]. Consistent improvements require iterative adaptation to the local context therefore greater scientific rigour is needed in the application and reporting of these methods [18].

Despite the challenges in its most effective application, PDSA cycles have been used successfully [19–21]. The strength of the PDSA cycle is the iterative approach to test and assess an intervention rapidly and make necessary changes timely [18]. The present study will use the Model for Improvement and the PDSA cycle to improve FCC in our level III NICU.

An urgent need is seen to standardize FCC interventions and core outcome measures to enable future comparison of the efficiency of FCC interventions and thus to improve the evidence base [12]. These outcome measures need to involve the infant, the parents and the medical team, as all are closely linked and interdependent.

Therefore, a comprehensive standardized assessment tool assessing the advances of parent, infant and staff outcome in the context of the degree of FCC implementation was developed. The aim of the present study is to test this new assessment tool in a prospective single centre longitudinal cohort study.

## Methods/design

The study design is a prospective single centre longitudinal cohort study as the enhancement of FCC primarily is a change in unit culture and the attitudes of individuals [7].

### Inclusion and exclusion criteria

#### Inclusion criteria for infants

Inborn and outborn preterm infants of ≤ 32 + 0 weeks of gestational age (GA) and/or birthweight ≤ 1500 g will be included in the study after legal guardian written informed consent.

#### Exclusion criteria for infants

Exclusion criteria are severe congenital anomalies (e.g. cyanotic heart disease, severe lung hypoplasia, congenital diaphragmatic hernia), decision not to provide full life support, decision for palliative care before study entry, or parents with severe psychiatric disease.

While the intervention includes all infants admitted to the neonatal unit, only those infants meeting inclusion criteria and not meeting exclusion criteria are eligible for the study.

#### Inclusion and exclusion criteria for staff

Inclusion criteria for medical staff is being a registered member of the medical team (doctor, nurse) at the neonatology department of the University Hospital Giessen, Giessen, Germany. Exclusion criteria are decline of informed consent.

The baseline cohort will consist of 45 preterm infants and their parents. Subsequent cohorts will consist of all included infants who will be recruited consecutively over 6-month-periods together with their parents. The expected number of eligible patients is 90 patients/year based on average admission during the last 5 years (2016–2020).

### Process of informed consent

All parents who’s preterm infant are meeting the inclusion criteria will be approached. Legal guardians will be asked for informed consent by good clinical practice (GCP) qualified staff members.

The study was designed in accordance with the declaration of Helsinki and approved by the Ethics Committee of Justus Liebig University, Giessen, AZ 153/20. The protocol has been registered at clinicaltrials.gov (No NCT05286983).

### Setting

The neonatal department of the University Hospital Giessen is a tertiary care 10 beds NICU together with a 27 beds step-down unit on the same floor. The step-down unit includes 8 rooming-in beds designed as double rooms with an accompanying bathroom (2 mother or father-infant- dyads per room).

### First step towards establishment of FCC

In 2017/2018 the Family Infant Neurodevelopmental Education (FINE) program was introduced as a first step to enhance FCC in the unit. The FINE programme is designed to provide a theoretical framework and practical skills to neonatal professionals based on three principles: neuroprotection, relationship and individualized care [22, 23].

### Forming the focus group

A multidisciplinary focus group including staff nurses and physicians with a special interest in FCC will be established to guide the whole project of enhancing FCC in the NICU, as a next step a member of the psychosocial support team will be included in the focus group. Including parents in FCC focus groups has been suggested to be beneficial [24] and is one of the future goals.

The focus group will meet regularly and will decide on FCC interventions as potentially better practices (PBPs). The PBPs will cover the four pillars introduced by FiCare: parent education, staff training, NICU environment and psychosocial support [13]. The team will then disseminate the changes into the greater team through workshops, hands-on teaching, displays, etc. Potential PBPs for our department enclose: Implementation of a parent education program, parent participation on rounds, parent presence during handover, parent skill self-assessment, systematic parent-to-parent support, implementation of a parent advisory board, participation of parents in the focus group, implementation of the CO- PARTNER tool to enhance and measure parent participation and collaboration with the medical team, [25] implementation of regular staff education, improvement of psychosocial support, improvement of neonatal unit surroundings to promote parent-infant-closeness.

### QI Method for Implementation

The Model for Improvement and the PDSA (Plan- Do- Study- Act) cycle will be used as QI Method to improve FCC in our level III NICU as it allows rapid tests of change and improvement of outcomes [16].

Every 6-months period 1–3 new PBPs will be introduced by the FCC team and evaluated using 2–3 repetitive PDSA cycles. Although PDSA cycle time intervals of 4 weeks or shorter have been recommended to track change in a “live system”, slightly longer time intervals were chosen as the implementation of change in a NICU setting with working in shifts slows down dissemination of change [18].

### Degree of FCC

Two different tools will be used to assess the extent of FCC implementation. The first tool asses the implementation of FCC on an organizational level and was designed by the Institute for Family Centred Care: The Self-assessment inventory of family centred newborn care [26], it was shortened and translated into German language following the guidelines for translation and cultural adaptation to assess FCC in general [27].

The second tool has been published by the FINE group [28] and focuses on the operational implementation of FCC on a daily basis.

### Infant outcomes

The primary outcome of the present study is the length of hospital stay measured by corrected gestational age (cGA) at discharge.

The secondary outcomes are presented in Table 1.

**Table 1 Tab1:** Secondary outcomes

Neonatal morbidities	Bronchopulmonary dysplasia as defined by Walsh [29] Intraventricular hemorrhage ≥ Grade 3 and cystic periventricular leukomalacia as diagnosed by ultrasound [30] NEC ≥ Stage 2 [31] ROP ≥ Stage 3 or treatment of ROP
Growth	Weight gain (g/kg/d) from admission to 36 + 0/40 + 0 weeks (cGA) Z- Scores for weight, length and head circumference at 36 + 0 weeks, 40 + 0 weeks, and 3, 12 and 24 months (cGA)
Nutrition	Day of Life (DOL) of achievement of full enteral feeds defined as 150 ml/kg/d for 3 consecutive days Removal of iv access (DOL) Removal of nasogastric tube (cGA) Breast milk nutrition (Percentage of breast milk within DOL 1–14, DOL with first breast milk feed, DOL with full breast milk feed, breast milk proportion at discharge, fully breastfed at discharge
Respiratory support	End of Continuous Positive Airway Pressure (CPAP) End of Highflow Nasal Cannula (HFNC) End of oxygen supplementation
GA at start of rooming- in	
Neurodevelopmental long-term outcome	Neuropsychological Developmental Screening (Neuropsychologische Entwicklungsscreening, NES, 2005) at 12 months cGA Bayley Scales of Infant Development, 3^rd^ Edition, German Version, at 24 months of cGA Gross Motor Function Classification System (GMFCS)

### Parental outcomes

#### Parental mental health

Depression and anxiety scores of mothers and fathers will be evaluated using standardized questionnaires within the first 10 days after birth, after 4 weeks, at discharge, at 3, 12 and 24 months (corrected age of the preterm infant [32]. Depression and Anxiety score is evaluated with the German version of the Hospital and Anxiety and Depression Scale (HADS-D). The HADS-D is a validated self-report questionnaire divided into 2 sub-scales (anxiety and depression HADS sub-scales) designed to measure recent depression and anxiety symptoms and has been used for evaluation of NICU parents with a cut-off score of 8 or above for both subscales indicating clinically significant anxious or depressive symptomatology [33, 34].

For evaluation of parenting stress, the Parenting Stress Index (PSI), German Version (Eltern-Belastungs-Inventar, EBI) will be used at 3, 12 and 24 months (corrected age). The PSI has been used to evaluate parenting stress in mothers of very preterm infants up to the age of 24 months corrected age [35, 36].

#### Parental satisfaction with care and parental skills

For the evaluation of parental satisfaction with care, a questionnaire has been designed covering relevant areas such as NICU surroundings, visiting hours, medical care, or communication.

Parental skills will be parent self-assessed with a newly developed questionnaire focussing on discharge readiness and competence at home. Parental satisfaction with care and parental competences are important components of FCC.

#### Parent-infant-interaction

Charts and tables at the bedside will be used to assess the degree of parental involvement in the care of the infant (e.g. feeding, bathing, etc.) during the hospital stay and to be able to analyse whether parental involvement increased during the intervention.

Parents being the primary caregiver of their infant are at the core of FCC [6]. This includes being actively involved in the nursing care from admission onward, being involved in decision making and being able to visit the infant unrestrictedly.

#### Parental visiting hours

Visit duration and time spent kangarooing will be recorded separately for mothers and fathers.

### Staff outcome

Satisfaction of the medical team with the work environment will be evaluated using part of the German version of the Copenhagen Psychosocial Questionnaire (COPSOQ). The COPSOQ is a valid and reliable tool for workplace satisfaction surveys [37]. Workplace satisfaction will be evaluated every 6 months.

### Timeline

The current status (baseline data) will be assessed in a baseline cohort of 45 preterm infants and their parents, as this is the average number of patient admissions per 6 months fulfilling the inclusion but not meeting the exclusion criteria during the last 5 years. The following cohorts will consist of all included infants who are recruited consecutively within 6-month-periods and their parents. The duration of the study will be 5.5 years with the first interim analysis after 2 years of start of the first intervention phase. A study period of 5.5 years for recruitment was chosen because shorter time periods have been associated with lacking results [7].

### Statistical assessment

Trend analyses and process- control charts (Sample Process Control Chart, Fig. 3) will be used for outcome assessment as used previously in quality-improvement studies [38].

**Fig. 3 Fig3:**
[figure not shown]
Process control chart

Process control charts will be used to describe, visualize, detect and understand changes in processes of care and outcomes [39]. Crude rates or medians will be plotted using 6-month periods to provide sufficient time points for process control chart analysis while maintaining more than 40 observations for subgroups [39]. For each graph, upper and lower control limits will be determined using standard statistical process-control parameters (± 3 standard deviations) using 6 months baseline data. We aimed to have 21 data points. Special-cause variation in outcomes will be defined as (significant changes that are not part of random variation) as any data point beyond the control limits, or 6 sequential points on 1 side of the mean, in either direction [38].

Second, linear trends for changes in FCC care practices, patient characteristics, and outcomes will be analyzed using F or Wald χ2 tests from linear or logistic regression models with 6 months periods used as continuous variable. Models will be adjusted using a generalized estimating equation approach (to account for clustering) with symmetric covariance structure, for the common variables known to be associated with the outcomes: e.g. gestational age in weeks (as a categorical variable), sex, demographics, multiple births, small for gestational age, outborn status, Score for Neonatal Acute Physiology version II (SNAP II) greater than 20, antenatal steroids, and change in major medical interventions. Change in major medical interventions was included because there may be future changes such as general stem cell transplantation or artificial placenta, which may have a tremendous effect on the long term outcome.

Data management and statistical analyses will be done using Microsoft^R^ EXCEL and R version 3.2.2 A 2-sided p value of less than 0.05 will be regarded as statistically significant. Data imputation will be done by study nurses and students and cross checked by the GCP qualified investigators. Source data will remain within the study site.

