### Sample size calculation

#### Primary outcome: corrected GA at discharge

A sample size of approximately 110 parent/child dyads is required to achieve a power of 95% in a single factor analysis of variance with cGA as dependent variable and implementation status of Fine + criteria as independent variable with a global significance level of 5% when comparing 11 implementation levels/time points to prove a reduction in cGA at discharge of two weeks. The expected number of at least 300 enrolled infants (very conservative estimation) will be sufficient to prove the targeted reduction in cGA and to compensate for unknown parental study compliance and unexpected drop-outs.

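### Control charts referenced to one 45-infant half-year would signal special cause in about 41–49% of charts when nothing has changed

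*Protocol article*

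**What the plan says.** The Statistical assessment section names trend analyses and process control charts as the methods for assessing outcomes. For the charts it fixes the following:

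- Plotted statistic: "Crude rates or medians will be plotted using 6-month periods", with the aim of "maintaining more than 40 observations for subgroups".
- Limits: "upper and lower control limits will be determined using standard statistical process-control parameters (± 3 standard deviations) using 6 months baseline data".
- Signal: "any data point beyond the control limits, or 6 sequential points on 1 side of the mean, in either direction". The plan defines a signal as a significant change that does not belong to random variation.
- Number of points: 21 are aimed at. Recruitment of 5.5 years in half-year periods gives 11, and the Sample size calculation also works with 11 levels.

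The Timeline section gives the size of the reference: "The current status (baseline data) will be assessed in a baseline cohort of 45 preterm infants and their parents". The same number stands under the inclusion criteria.

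The text does not say where the mean in the run rule comes from, or whether the SD is that of individual infants or of the plotted rate or median. A separate linear trend regression with covariate adjustment follows, tested at two-sided p < 0.05.

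**The concern.** One point per half-year and six months of baseline make the baseline one point. A single point gives no information on ordinary variation between half-years. Its sampling error is also as large as that of every later point. If it falls high by chance, all later points tend to fall below it, and a run of 6 on one side follows easily without any change in care.

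The Discussion relies on the charts to separate natural variation from variation caused by the interventions. If a chart often signals when nothing has changed, it cannot do that for the outcomes charted this way.

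**Working it through.** The plan gives no false-signal rate or detection probability for the charts, so there is no figure of its own to reproduce.

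**Inputs.** Baseline 45 infants (Timeline). Later points of 45 infants (90 eligible per year), or about 27 if only the minimum of 300 is enrolled (300/11 = 27.3). Ten later points (11 − 1), or 20 if 21 points are meant. SD of corrected gestational age at discharge 2.1 weeks, or 4.0 with the five late discharges included (Sample size calculation, Background). Assumed: the centre line is the baseline value, and limits are ±3 standard errors of the plotted statistic.

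**Run rule, exact, 45 infants per point.** Given the baseline value, each later point falls above it with probability p. With equal sizes and no change, p is uniform on (0, 1). A run of at least 6 above the line in 10 points starts at point 1 (p⁶) or at one of points 2 to 5 ((1 − p)p⁶ each). Doubling for runs below the line:

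2 × ∫ p⁶[1 + 4(1 − p)] dp = 2 × (1/7 + 4/56) = 3/7 = 43%.

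With a known centre line p = 1/2, and the same expression gives 2 × (1/64) × 3 = 9.4%.

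**Both rules, by simulation, no true change.**

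| Setting | Beyond limits | Run of 6 | Either |
|---|---|---|---|
| 45 per point, 10 later points | 23% | 43% | 49% |
| 27 per later point, 10 later points | 16% | 35% | 41% |
| 45 per point, 20 later points | 34% | 65% | 70% |
| Known centre line, 10 later points | 2.7% | 9.4% | 12% |

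Medians give the same 49% as means, skewed data 48–50%, and binary rates between 5% and 30% give 41–48%. An assumed between-period intraclass correlation of 0.01 raises 49% to 59%. With 20 later points of about 22 infants the rate is 61%. A known centre line with 20 later points would itself give about 27–28%, so part of the 70% comes from the longer chart.

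**Size of the reference.** With 45 per later point and 10 later points, either rule fires in 37% with a baseline of 90 infants, 27% with 180 and 19% with 450. Widening the limits by √2 to allow for the error of a 45-infant baseline cuts limit crossings to about 3%, but the run rule keeps the total at 43%. The run rule around a noisy line is therefore the main cause.

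**Meaning of ±3 SD.** With the SD of individual infants, the limits are 3 × 2.1 = ±6.3 weeks, or 3 × 4.0 = ±12.0. With the standard error they are 3 × 2.1/√45 = ±0.94 weeks for a mean, and 1.2533 × 0.94 = ±1.18 for a median.

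**The case against.** **The centre line is inferred.** This objection stands as a limit on the size. If runs are counted about the grand mean while the limits stay on the baseline, the rate is about 25–26%. If both are centred on the grand mean it is about 7%, but that is hard to reconcile with limits set from baseline data.

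**The charts are not the confirmatory test.** The plan uses them to describe and visualise as well as to detect, the p < 0.05 test belongs to the trend regression, and the sample size rests on an analysis of variance. A reader might infer that about half of such studies would reach a false conclusion. The documents do not support that: the rate is per chart, and no passage makes a decision on the primary outcome depend on a chart signal. What remains is that the plan gives a signal its own meaning of non-random change.

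**Detection of the target.** A reader might also infer that the limits can never show the two-week reduction. That needs ±3 SD to mean the SD of individual infants, which is unlikely: the text speaks of standard process-control parameters for plotted rates or medians. Even then the run rule detects the shift at SD 2.1 in 95% (linear decline) to over 99.9% (immediate step), though in only 51% if the shift covers just the last five periods. With standard-error limits for medians, the limits alone detect it in 98–99.9% at SD 2.1. This is an ambiguity to resolve, not a demonstrated failure.

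**Other outcomes.** Staff satisfaction is surveyed repeatedly in one team, so the figures for independent groups of 45 do not carry over to it.

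**Conclusion.** The point holds as a defect of the stated chart rules. With a baseline centre line, 3-standard-error limits and no true change, a chart signals in about 41–49% of cases with 10 later points and about 70% with 21 points in all, against about 12% for 10 later points around a known line. The calculation assumes independent infants and no real variation between half-years; such variation would raise the rate. Because the rules themselves produce these signals, this is more than omitted detail. It does not affect the error rate of the trend regression.

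**What to change.** 1. **State three things:** the centre line used for both limits and runs; that ±3 SD means the standard error of the plotted statistic; and whether 11 or 21 points are planned.
2. **Enlarge the reference for routinely recorded infant outcomes.** Pool several half-years after FINE and before the study, restricted to infants who meet the study criteria, and check first that they are stable. The whole of 2016–2020 is unsuitable, because FINE was introduced in 2017/2018 and the Discussion treats it as the baseline. The 2018–19 discharge figures in the article concern VLBW infants, so they would need re-extraction for the study criteria. Four half-years of 45 reduce the rate to about 27%.
3. **Let the limits include the baseline's own error.** For a mean with 180 reference infants: 3 × 2.1 × √(1/45 + 1/180) = ±1.05 weeks. The rate then falls to about 24%.
4. **Treat chart signals as descriptive.** The rate stays above the 12% of a known line, and parent and staff outcomes may have no history. Base claims of change on the adjusted trend model.

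An 8-point run rule is optional. With four pooled half-years and limits not widened as in step 3, it lowers the rate from 27% to about 15%. However, a shift that starts at the fourth of 10 later points leaves only 7 shifted points, so the run rule often misses it and detection falls to the limits. That matters in a stepwise rollout.

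The cost is retrospective data extraction, a few sentences of text and weaker claims from the charts.

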The COVID pandemic starting at the beginning of our study was a big challenge as access to hospitals was greatly restricted in Germany also for the parents of NICU patients. Our results might give further insight into the consequences of these restrictions for the infant, parents and staff.

There are as well limitations to our study. The study is a single centre study undertaken in one neonatology department in Germany. The context of the particular neonatology department involved and its patient demographics including the socioeconomic and cultural background will influence the results. Due to the single center design the number of patients is restricted and a recruitment period of 5.5 years is needed. Changes of e.g. nurse-patient ratios on the basis of modifications of the obligatory national guideline of the Joint National Committee of Germany or towards the provision of active support according to the national AWMF guideline recommendations for the care of preterm infants at the border of viability will have an impact on the study results. Possible demographic changes over the study duration will also affect results. Nevertheless, our study pioneers the comprehensive evaluation of infant, parental and staff outcomes and when implemented successfully, the studied comprehensive assessment tool can be used to monitor and guide FCC interventions within a local or multicentre context in any other NICU.

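### The trend models name SNAP II as a yes/no covariate cut at 20; entering the full score would recover discarded information at almost no cost (minor)

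*Protocol article*

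**What the plan says.** Statistical assessment describes "linear or logistic regression models with 6 months periods used as continuous variable", adjusted through generalized estimating equations "for the common variables known to be associated with the outcomes: e.g. gestational age in weeks (as a categorical variable"), followed by "sex, demographics, multiple births, small for gestational age, outborn status", then "Score for Neonatal Acute Physiology version II (SNAP II) greater than 20", antenatal steroids and change in major medical interventions. The significance rule is "A 2-sided p value of less than 0.05 will be regarded as statistically significant".

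Gestational age therefore keeps week-by-week resolution, while SNAP II is reduced to two categories. No reason for the cut is given. The article reports no SNAP II distribution, no share of infants above 20 and no association of SNAP II with discharge age.

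The limitations in the Discussion say that results may be affected by changes in nurse-patient ratios, by changes "towards the provision of active support according to the national AWMF guideline recommendations for the care of preterm infants at the border of viability", and by demographic changes.

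**The concern.** The study is a single-centre cohort without a concurrent control, and the effect on discharge age is read from a slope over 6-month periods. The control charts plot crude rates or medians, so covariate adjustment in the trend models is the main protection against changing case mix. Both uses of a severity covariate suffer when it is cut in two.

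- **Precision.** A yes/no term explains less of the outcome variance than the score it was made from, so the slope has a larger variance. This needs no drift.
- **Confounding control.** Scores of 0 and 20 are treated as equal, and so are 21 and 60. If severity changes over time within those two groups, the term cannot remove the change.

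What is at stake is a somewhat less precise slope and, conditionally, a small spurious component in it.

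**Working it through.** **The plan's own figure.** Sample size calculation says "A sample size of approximately 110 parent/child dyads is required to achieve a power of 95% in a single factor analysis of variance", "when comparing 11 implementation levels/time points to prove a reduction in cGA at discharge of two weeks". Reading the lower stated effect size of 0.5 as Cohen's f, with 11 groups and alpha 0.05, a noncentral F calculation needs N = 108, or 110 when balanced at 10 per level. Power at 110 is 95.7%. The figure reproduces on that reading. It involves no covariate, so this point does not change it.

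**Inputs from the article.** Binary SNAP II term; period as a continuous variable; 11 levels; at least 300 infants expected; 2-week target.

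**Assumptions, none in the article.** Share p above 20: 5-50%. Partial correlation r of SNAP II with discharge age given the other covariates: 0.3-0.5. Severity drift over the study: 0.5 SD. Effect on discharge age: 0.5-1 week per SD of severity.

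**Step 1: information kept by the cut.** For a normal score with linear effect, k = phi(z)^2 / [p(1-p)], where z is the upper-p normal quantile.

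| Share above 20 | Kept, k | Lost, 1-k |
|---|---|---|
| 5% | 0.224 | 78% |
| 10% | 0.342 | 66% |
| 20% | 0.490 | 51% |
| 30% | 0.576 | 42% |
| 50% | 0.637 | 36% |

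Half or more is lost only if about 21% or fewer infants lie above 20. For right-skewed gamma scores (shapes 0.7 to 4) with 10-50% above the cut, the loss is 35-57%, mostly below half.

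**Step 2: variance of the slope.** With no severity drift, the ratio of slope variances, cut against full score, is (1 - r^2 k) / (1 - r^2).

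- Largest: r = 0.5, k = 0.224 gives (1 - 0.056) / 0.75 = 1.26.
- Smallest: r = 0.3, k = 0.637 gives (1 - 0.057) / 0.91 = 1.04.

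The standard error is thus about 2-12% larger (square roots 1.02 and 1.12). In effective numbers, 300 / 1.26 = 238 and 300 / 1.04 = 288 infants.

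**Step 3: bias if severity drifts.** A large-sample linear model (n = 2,000,000, 11 periods) was fitted with a gestational-age proxy and the binary term, with 10-50% above 20.

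- No drift: bias is zero to rounding.
- With drift, the share of the SNAP II confounding left in the slope is 36-67% when SNAP II is unrelated to gestational age, and 44-80% when their correlation is 0.5-0.7.
- At 0.5 week per SD, the unadjusted bias is 0.5 x 0.5 = 0.25 weeks. The cut leaves 0.25 x 0.363 = 0.09 to 0.25 x 0.797 = 0.20 weeks.
- At 1 week per SD, it leaves 0.5 x 0.363 = 0.18 to 0.5 x 0.797 = 0.40 weeks.

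These are totals over the whole study. They scale in proportion to the assumed drift and effect per SD.

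**The case against.** The strongest reply is that the list is introduced as illustrative, the document is a condensed article, and the final form of each covariate may be settled in an analysis plan that is not shown. That stands in part: one cannot say that SNAP II above 20 is the only severity information in the models. Gestational age by week, small for gestational age, outborn status and antenatal steroids carry some of it. But an illustrative list leaves open which further variables enter. It does not undo the form stated for this one.

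The second reply is that the consequence is small and conditional. That stands.

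Four stronger readings are tempting, and the article supports none of them.

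- **That at least half the information is lost.** This needs a near-normal score and about 21% or fewer infants above 20; skewed scores mostly lose less.
- **That most infants lie below the cut,** so the covariate hardly separates them. The article gives no SNAP II data for this cohort.
- **That the Discussion predicts the harmful drift.** A change in active support at the border of viability mainly shifts gestational-age composition, and demographics are also on the covariate list. The article says nothing about severity drifting within gestational-age week.
- **That the bias could approach half a week for a drift of only 0.3 SD.** Multiplying r = 0.5 by the overall SD of 4.0 weeks, by 0.3 and by 0.776 gives 0.47 weeks. This pairs a partial correlation with a marginal SD. If the other covariates explain 30-50% of the variance (assumption), it falls to 0.33-0.39 weeks, since 0.47 is multiplied by the square root of 0.7 or 0.5.

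It is also an inference that the raw score is stored. It must be computed to apply the cut, but the article does not say that it is retained.

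**Conclusion.** The point holds as a minor one. The plan states a yes/no cut for the only physiological severity score that it names, gives no reason, and thereby discards roughly a third to three quarters of the score's linear information under the assumed shares. The consequence that needs no drift is a modest loss of precision: about 4-26% in the variance of the period slope, if SNAP II has a partial correlation of 0.3-0.5 with discharge age.

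Bias is a separate and conditional matter. It arises if, and only if, severity drifts beyond what the other covariates capture. Under the assumed drift it is about 0.1-0.4 weeks, at most a fifth of the 2-week target (0.4 / 2), though it would weigh more against a smaller estimated trend. Its direction cannot be known in advance. It would be wrong to conclude that the discharge-age trend is confounded by severity; the article gives no evidence either way. The article does not contradict itself on this point, and the stated sample size is unaffected.

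**What to change.** In Statistical assessment, replace the dichotomised term by the SNAP II score as a continuous covariate: a linear term plus one spline term (for example three knots) in the linear models, and a linear term alone in the logistic models. Keep the cut at 20 for descriptive tables.

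The cost is one phrase of text and about one extra degree of freedom in the linear models, with none in the logistic models. The raw score must be retained in the data set; if only the indicator has been stored, the score has to be taken again from the source records. The change is best made and dated before the outcome trends are analysed.
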